### Eligibility criteria (inclusion and exclusion)

The women with the following pathologies or special situations was excluded from the study: Type 2 Diabetes, being or trying to become pregnant, being in a maternal lactation period, suffering from kidney failure, being under age, presenting a healthy weight (BMI ≤ 25) or receiving pharmacological antidepressant treatment. Women not possessing smartphones with Android or iOS operating systems and those without available data connections did not participate in the study.

Also, with the aim of homogenizing the study population, the inclusion criteria were: having a body fat percentage of ≥30%, being sedentary, defined as low energy sitting (or reclining) during waking hours [36], and not having been submitted to a restrictive diet in the 6 months prior to the beginning of the study. The flow chart of the participants is found in Fig. 1.

**Fig. 1 Fig1:**
[figure not shown]
Flow chart of the participants

### Study variables and measurements

#### PUSH notifications

Figure 2 shows the implementation of the PUSH notifications in the study design. Automatic PUSH notifications were scheduled to be sent on specific days, or not, with personalized health and motivation messages, which was aimed to provide comments for reinforcing behavior modification and encouraging interaction with the APP. These comments were based on the following behavioral theories:
Health tips, where the primary tailoring goals were: attention and peripheral processing [37].Physical Activity Tips, in this case: attention and being informed [38].Self-monitoring tips, where the primary tailoring goals were: decision making and behavioral intention [39].

**Fig. 2 Fig2:**
[figure not shown]
Implementation of the PUSH notifications in the study design

Three specific times were established throughout the day for the sending of messages. According to previous works [38, 39], the best time for sending PUSH notifications was depended on: a) when patients were able to fix their preferred time for receiving them, b) trying to deliver them at times that did not interrupt the daily routine (notifications were more effective) [40]. For these reasons, it was determined that the best adherence was achieved at the times of day at which there were no commitments (before work, during lunch, before supper), so we fixed for 8.30 a.m. (point 1), 14.00 p.m. (point 2) and 20.00 p.m. (point 3). The first message was sent between points 1 and 2, and those users who do not answer it again received an automated notification in point 3.

The App Nutrición Sur (Fig. 3) sent automatic notifications (see architecture in Fig. 4) programmed to receive on concrete days, with personalized messages on health and motivation. The contents of the messages were extracted from a previously established library that is consistent with advice related to food consumption and physical activity. This section aimed to stimulate and remind the patient about the protocol assigned, encourage her to complete a specific steps objective (that she should be reported in the App), or carry out a session at her sports center. Also, the App included a Self-monitoring menu in which the patient could give her opinion on the diet proposed, on doing the physical activity prescribed and on her body weight, measured on home scales. The objective was to determine the effect of the PUSH notifications on compliance with the intervention protocols, as well as the changes in body composition. The information supplied in the two previous measures appeared in real-time on the researcher’s internet control panel.

**Fig. 3 Fig3:**
[figure not shown]
Screenshot of the APP developed for the research project (Nutrición Sur version 15.0.0)

**Fig. 4 Fig4:**
[figure not shown]
PUSH notifications architecture

#### Body composition

The percentage of body fat (BF), muscle mass (MM), and the percentage of water (W), considered to be result variables, were monitored and collected throughout the time by previously validated multifrequency bioelectrical impedance (BWB-800A, Tanita Corp. USA) [41]. This method is based on a 3-compartment model capable of evaluating BF, MM, and bone mineral content. Also, the percentage difference of each dependent variable was calculated throughout the weekly consultations, taking as a reference that recorded in the first one.

Likewise, the following independent variables were noted: age (years), height (cm), weight (Kg), and BMI (Kg/m2). The anthropometric measurements were taken following the recommendations in the standardized anthropometry handbook [42] by experienced personnel to diminish the coefficient of variation. Each measurement was taken three times, calculating the mean value. All the quantitative variables were measured with a precision of 0.1. For the height, a stadiometer (SECA 213) was used.

#### Physical activity

The strata proposed by Matthews [43] to evaluate the physical activity was employed. The MPA and IPA patients received instructions for doing aerobic exercises corresponding to a training-induced energy expenditure of approximately 300 to 600 kcal/day, while those relating to the LPA group did not receive any instructions in this respect. For the activity of MPA subjects, the women walked between 30 and 60 min daily or carry out a volume of steps of between 7500 and 10,000. To be considered as IPA individuals, the patients must undertake three times a week, intense physical activity sessions, above 70% of VO2max. Their heart rate (HR) was calculated using the Karvonen formula [44], and the maximum HR determined by the formula: 220 – age (years). Adherence was monitored by weekly exercise records completed by participants and researchers. In the MPA group, the controls were made by installing a pedometer (ACCUPEDO) via a mobile telephone application. The patient had to show her records weekly. The IPA group patients trained in the facilities of any sports center of their choice and can select among a variety of intense PA programs (CrossFit or Body Pump), which they visited three times a week, as well as completing the same steps objective of the MPAs.

#### Diet pattern

Concerning diet, the daily energy requirements was determined by estimating energy expenditure while at rest through the formula proposed by Harris-Benedict (655.0955 + 9.5634 [Weight (kg)] + 1.8496 [Height (cm)] – 4.6756 [Age (years)] [45] and multiplying the value obtained by a factor of 1.5 in those patients who were performing physical activities [46]. All the participants followed a dietary regime for 24 weeks with the following allocation of macronutrients: 25–30% proteins, 40–45% carbohydrates, and 30–35% fats. A hypocaloric diet was designed with a reduction of 500 kcal/day during the treatment period to obtain a weekly weight loss of 400 g. No vitamins or other nutritional complements are prescribed. After being included in the study, each woman took part in a 1-h seminar, in which a Dietitian-Nutritionist instructs them on the suitable selection and preparation of food. The menu proposed will be valid for seven days. The energy and nutritional supply were evaluated by the program Dietowin® and the weighing method [47].

The follow-up tests began the first week that the diet and physical activity were assigned. The body composition was measured after the night fast. Patients attempted to the clinic on the same day of the week, at the same time, and to wear the same clothes. The revision appointments continued at a weekly frequency up to week 24.

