## Methods/design

### Study design

A controlled randomized three-armed clinical trial was conducted that includes a physical activity lasting six months in women following the same dietary prescription. The groups were differentiated based on whether or not they received Push notifications from a mobile application (Nutrición Sur version 15.0.0). Thus, the control group did not receive these notifications, whereas the women who received them constitute an experimental group. Additionally, inside each group, three different subgroups were randomly established with distinct degrees of physical activity (PA) intensity; these could be light (LPA), moderate (MPA), or intense (IPA).

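### The written energy rule ties calorie allowance to the randomised activity level, so the LPA versus MPA/IPA comparison mixes activity with diet

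*Protocol article*

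**What the plan says.** Three sections of the protocol article bear on this.

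- **Study design.** The trial "includes a physical activity lasting six months in women following the same dietary prescription". Activity level is assigned at random within the PUSH and control groups: "inside each group, three different subgroups were randomly established with distinct degrees of physical activity (PA) intensity". The levels are light (LPA), moderate (MPA) and intense (IPA).
- **Physical activity.** MPA and IPA women are instructed to do aerobic exercise with a "training-induced energy expenditure of approximately 300 to 600 kcal/day", while "those relating to the LPA group did not receive any instructions in this respect".
- **Diet pattern.** Resting expenditure comes from a Harris-Benedict equation in weight, height and age. The requirement is then found by "multiplying the value obtained by a factor of 1.5 in those patients who were performing physical activities". For the diet itself, "A hypocaloric diet was designed with a reduction of 500 kcal/day", with an intended loss of 400 g per week. The macronutrient split and the 24-week duration are common to all women.

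No multiplier is given for women who are not performing physical activities. The Discussion names the course of body composition by PUSH notification and by prescribed activity as the second general objective.

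**The concern.** All women enter sedentary, and activity level is allocated at random. If the 1.5 factor goes only to women with an exercise prescription, the same allocation also fixes how much energy a woman may eat. LPA versus MPA or IPA is then a comparison of two things that change together.

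That matters for the second objective. The Discussion says the results should help professionals set goals when prescribing physical activity. A reader who takes the Study design section at its word will credit a difference between LPA and the active levels, or its absence, to exercise. If the extra allowance is larger than the energy spent in training, LPA women have the larger deficit by prescription, and a benefit of exercise on body fat could be hidden or appear reversed. If it is smaller, the distortion is milder or runs the other way. Either way, the deficit need not be the single 500 kcal/day that the Diet pattern section states for everyone.

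**Working it through.** The protocol gives no kcal prescription per activity level, so there is no stated figure to reproduce. The check applies the protocol's own rule.

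**Inputs from the protocol.** Harris-Benedict equation, factor 1.5, reduction of 500 kcal/day (Diet pattern); training expenditure of 300 to 600 kcal/day (Physical activity); age 25–64 years (Background); BMI above 25 (Eligibility criteria).

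**Assumptions.** The LPA factor f is not stated. The literal reading is f = 1.0; 1.2 and 1.375 are used only to show sensitivity, not as candidates for the right value. Body sizes are assumed: an example woman of 75 kg, 162 cm and 40 years, and a grid of heights 150–175 cm and BMI 25.1–39.1 over the stated ages. Non-exercise activity is taken as equal across levels.

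**Formulas.**
- REE = 655.0955 + 9.5634 × weight + 1.8496 × height − 4.6756 × age
- Allowance for MPA/IPA = 1.5 × REE − 500
- Allowance for LPA = f × REE − 500
- Gross gap = (1.5 − f) × REE
- Net gap (extra deficit for LPA) = gross gap − training expenditure

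**Example woman.** REE = 655.0955 + 717.255 + 299.635 − 187.024 = 1485 kcal/day. The MPA/IPA allowance is 1.5 × 1485 − 500 = 1727 kcal/day. With f = 1.0 the LPA allowance is 1485 − 500 = 985 kcal/day. The gross gap is 0.5 × 1485 = 742 kcal/day. The net gap is 742 − 600 = 142 to 742 − 300 = 442 kcal/day.

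**Grid corners.**
- Smallest: 150 cm, BMI 25.1 (56.5 kg), 64 years. REE = 655.1 + 540.1 + 277.4 − 299.2 = 1173, half of which is 587.
- Largest: 175 cm, BMI 39.1 (119.7 kg), 25 years. REE = 655.1 + 1145.2 + 323.7 − 116.9 = 2007, half of which is 1004.

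**Sensitivity to the unstated LPA factor (kcal/day).**

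| LPA factor (assumed) | Gross gap, example | Net gap, example | Gross gap, grid |
|---|---|---|---|
| 1.0 (literal) | 742 | 142 to 442 | 587 to 1004 |
| 1.2 | 445 | −155 to 145 | 352 to 602 |
| 1.375 | 186 | −414 to −114 | 147 to 251 |
| 1.5 (same as active levels) | 0 | −600 to −300 | 0 |

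A negative net gap means that the active levels have the larger deficit. In the last row that difference is simply the training expenditure, with no dietary component.

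For the example woman, the gross gap equals 600 when f = 1.5 − 600/1485 = 1.10, and equals 300 when f = 1.5 − 300/1485 = 1.30. Below about 1.10 the allowance exceeds the whole stated training range; above about 1.30 it falls short of all of it. Even at f = 1.0 the smallest woman on the grid has a net gap of 587 − 600 = −13 at the top of the training range.

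**The case against.** The strongest reply is that the phrase about a common diet cannot mean equal calories, because the formula already varies by weight, height and age. It can be read as one common rule: same equation, same macronutrient split, same 500 kcal/day reduction, same duration, same weekly target. A larger allowance for women who exercise would then be an intended replacement for energy spent. That reading is fair, and it softens the conflict with the Study design section. It does not remove the problem: on the literal factor, the example woman's extra allowance exceeds the training energy it would replace, so the deficit is not equalised.

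A second reply is that the protocol never says the LPA factor is 1.0, and that light activity might itself count as performing physical activities, which would leave no gap. The Physical activity section, where LPA women get no exercise instructions, points the other way but does not settle it. This reply stands as a limit on size and direction.

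Two stronger readings are therefore tempting but unsupported. A reader might infer that the extra allowance always exceeds the training expenditure, or that the diet necessarily works against the active levels. Both hold only for LPA factors near 1.0, and even there not at every body size. A reader might also infer that the primary PUSH comparison, or the comparison of moderate with intense exercise, is compromised. Activity is randomised within each PUSH group, so PUSH versus control is not biased if the levels are balanced. MPA and IPA share the 1.5 factor, so the rule creates no difference between them.

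Finally, the Statistical analysis section already plans adjusted regressions for PUSH. Their covariates may be listed in a document not shown, and no omission is alleged.

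**Conclusion.** The concern holds in a limited form. Under the rule as written, the randomised activity level also sets the energy allowance, so LPA versus MPA/IPA compares activity together with a different diet. The size and sign of the resulting imbalance in deficit cannot be fixed from the article, because they turn on the unstated LPA factor. The intake gap is above zero for every assumed factor below 1.5, so the contrast is clean of diet only if LPA women receive the same factor.

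LPA versus MPA/IPA remains a valid randomised comparison of whole strategies. What fails is attributing its result to exercise alone. The figures assume prescribed rather than actual intake and expenditure, and equal non-exercise activity across levels.

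**What to change.** Reconcile the Study design, Physical activity and Diet pattern sections with the clinical team. State which factor applies to LPA women, which women count as performing physical activities, and whether the 500 kcal/day reduction is meant to give the same deficit at every activity level. Which rule is right is a clinical decision and is not proposed here.

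If the energy allowance does depend on activity level:

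1. Correct the Study design statement about a common diet, saying which elements are common and which vary.
2. Define LPA versus MPA/IPA as a comparison of activity-plus-energy-allowance packages.
3. Do not attribute differences in that contrast to exercise alone. MPA versus IPA needs no such caveat on account of this rule.
4. Include randomised activity level in the model for the PUSH effect, so that any imbalance between the PUSH groups is accounted for.

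The cost is a clarification of the text, one factor in the model, and a narrower interpretation of the activity comparison.

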### Statistical analysis

The quantitative variables were presented with the mean and the standard deviation, whereas the qualitative ones in frequencies and percentages. To contrast, the goodness of fit to a normal distribution of data from quantitative variables, the Kolmogorov-Smirnov test with the Lilliefors correction was used. For the bivariant hypothesis contrast, the two-means Student-t test was made, while, for the qualitative variables, the Chi-test and Fisher’s exact test was performed when necessary. Likewise, for the three or more means analysis, the ANOVA repeated means test was used to evaluate the effects of the intervention at the baseline moment, at 3 and 6 months, and the correlation between the quantitative variables was verified by Pearson’s (r) correlation coefficient. The ANCOVA analysis of covariance was applied to determine the effect of the baseline data on the modification of body composition. Finally, in the case of not fulfilling the criterion of normality or homoscedasticity, the non-parametric versions of the tests mentioned were conducted. Adjusted linear regressions were made for each variable of the body composition (%BF and MM) and the weight at the final moment of the study to estimate the standardized Beta coefficients possessed by the PUSH notifications in the achievement of objectives. For all the statistical analyses, an alpha error probability of under 5% (*p* < 0.05) was accepted, and the confidence interval calculated with a 95% security. For the statistical analysis, the computer program IBM SPSS Statistics version 22.0 will be used.

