### Sample size calculation

The primary outcome variable was fat mass loss after six months, and the anticipated minimum difference in the average fat mass loss was 2%, with an expected SD not exceeding 3.5% [35]. The study was designed to have at least an 80% power and an alpha level set at 0.5, obtaining a sample size of 27 individuals for each group (total *N* = 54). A total of 90 women (45 for each group), was estimated, to mitigate the effect of possible dropouts during this trial.

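### The named analyses drop women with missing visits by default and leave most weekly data unused, although the sample size allows for substantial dropout

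*Protocol article*

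**What the plan says.** Three parts of the Protocol article bear on this.

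- **Sample size calculation.** The requirement is given as "obtaining a sample size of 27 individuals for each group". It is then enlarged: "A total of 90 women (45 for each group), was estimated, to mitigate the effect of possible dropouts during this trial". No dropout rate is given.
- **Statistical analysis.** For three or more means, "the ANOVA repeated means test was used to evaluate the effects of the intervention at the baseline moment, at 3 and 6 months". The same section names Student t tests, an ANCOVA on baseline values, and adjusted linear regressions of final body fat, muscle mass and weight on PUSH, all in SPSS 22.
- **Diet pattern** and **Body composition.** "The revision appointments continued at a weekly frequency up to week 24". Change from the first reading is calculated for each body-composition variable at these weekly consultations.

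The article names no analysis set, imputation rule or missing-data method. A condensed article commonly leaves these to a fuller document, so their absence is not the complaint. The complaint concerns the tests that the article does name.

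**The concern.** Classical repeated-measures ANOVA needs every time point for every woman, and a test on final values needs the final value. Unless values are imputed, a woman who attends for four months and then leaves drops out of both, although she may have supplied some sixteen weekly readings. Enlarging the sample restores the number of completers but does not address who they are.

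Two things are at stake. The first is precision, because partial follow-up is discarded. The second is the PUSH comparison itself, because a contrast among completers is no longer protected by randomisation. Unequal loss is plausible here. The Background hypothesises better adherence with notifications, and the PUSH notifications section describes messages meant to motivate women and remind them of their programme. If that carries over to staying in the trial, the arms could lose different numbers of women or different kinds of women. The article does not say that it will.

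**Working it through.** **1. The plan's own figures.** The step from 27 to 45 reproduces at a 40% allowance: 27/(1 − 0.40) = 45, or 1 − 27/45 = 0.40. That is up to 18 women per group and 36 of 90.

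The 27 itself does not reproduce for a two-group comparison. With a difference of 2, SD 3.5, 80% power and two-sided 5%, n = 2 × (1.960 + 0.842)² × 3.5²/2² = 48.1, so 49 per group. That is a separate matter. Here 27 serves only as the plan's own number of women needed after dropout.

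**2. What each named method requires.** The ANOVA needs baseline, month 3 and month 6. The final-value regressions and t tests need the final reading. The ANOVA uses three time points from weekly follow-up to week 24.

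**3. Precision.** Assume a correlation of 0.7 between months 3 and 6, with all loss after month 3 and unrelated to outcome. Relative to the outcome variance, the variance of an arm mean at month 6 is:

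- completers only: 1/27 = 0.0370
- likelihood estimate that also uses the month-3 values of the women lost: (1 − 0.7²)/27 + 0.7²/45 = 0.51/27 + 0.49/45 = 0.0298

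Since 1/0.0298 ≈ 34, the all-data estimate is worth about 34 women per group instead of 27.

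**4. Bias.** The documents give no dropout pattern, so this is a simulation on stated assumptions: 4,000 trials, 45 per arm, SD of fat loss 2.5 at month 3 and 3.5 at month 6, correlation 0.7. Dropout occurs after month 3. Where it depends on outcome, women with less 3-month fat loss than their arm's average are likelier to leave (one logit per SD). The rates are those for a woman at her arm's average. The all-data estimate uses the 3-month values of dropouts.

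| Assumed dropout | True difference | Completer estimate | All-data estimate |
|---|---|---|---|
| 40% in each arm, same mechanism | 2 | 2.02 | 2.01 |
| 50% control, 30% PUSH, same relation to fat loss | 2 | 1.68 | 2.03 |
| 40% in each arm, related to fat loss in control only | 2 | 1.20 | 2.03 |
| 40% in each arm, same mechanism | 0 | 0.02 | 0.02 |
| 50% control, 30% PUSH, same relation to fat loss | 0 | −0.32 | 0.00 |
| 40% in each arm, related to fat loss in control only | 0 | −0.86 | −0.02 |

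Simulation error is about 0.95/√4000 = 0.015, so deviations of 0.01 to 0.03 are essentially noise. For a true difference of 2 the completer shortfall is nil, 0.32 (16%) and 0.80 (40%). Swapping the arms' roles reverses the sign of the bias, so exaggeration is as possible as dilution.

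The same runs qualify step 3. With dropout unrelated to outcome, the spread of estimates was 0.96 (completer) against 0.86 (all data), a variance ratio of 1.25 that agrees with 0.0370/0.0298 = 1.24. With outcome-related dropout the gain was small: 0.94 against 0.92, 0.95 against 0.95, and 0.94 against 0.89 in the first three rows.

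**The case against.** The strongest reply is that the article never commits to a completer analysis. A reader might infer from the list of tests that only completers will be analysed. The text does not say so. Excluding incomplete cases is how these procedures behave by default, every one of them can be run on imputed data, and an unseen analysis plan may provide for that. This stands, and it limits the point to the analyses run as named without imputation.

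Second, 40% is neither stated nor a forecast. It is the largest loss that the enlarged sample could absorb on the plan's own figures. This also stands.

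Third, a reader might infer that bias is near certain, or that randomisation is simply broken. The documents do not support that. Bias needs dropout to differ between arms in rate or in its link to fat loss. The article gives no such pattern, and weekly attendance is described without distinction by arm. Harsher assumptions than those above (about 50% against 25% dropout, in some runs with a stronger link to outcome in controls) bring the completer estimate to between 0.7 and 1.5, but nothing in the article favours them.

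Fourth, the planned ANCOVA and adjusted regressions partly address dropout that is related to baseline values. They do not address dropout related to early response.

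Fifth, choosing three time points in advance is legitimate in itself. That is true. The difficulty is combining this choice with a method that requires all three, when a large dropout allowance is planned and readings in between are already collected.

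**Conclusion.** The point holds in a limited form. The sample size makes room for losing up to 40% of women, an implied figure. The named ANOVA and final-value tests exclude women with a missing required time point by default and leave most weekly readings unused. Run as named without imputation, they give up information: about 27 instead of 34 effective women per group, if the correlation is 0.7 and all loss follows month 3 and is unrelated to outcome, and a smaller sacrifice if loss is related to outcome.

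They can bias the PUSH comparison in either direction if dropout differs between arms. With the same mechanism in both arms there is little or no bias. The completer estimates of about 2.0, 1.7 and 1.2 for a true difference of 2 illustrate the range under three assumed patterns; they do not predict this trial's result.

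A reader might also infer that weekly data would remove the problem. The all-data estimates recover the truth here because the simulated dropout depends only on observed 3-month values. Where loss depends on unobserved outcomes, a likelihood model does not remove the bias in general. The change is worth making before the analysis, but the text contains no false statement on this point.

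**What to change.** Replace the repeated-measures ANOVA with a linear mixed model for repeated measures of body fat.

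- **Women:** all those randomised, analysed in the arm assigned. Anyone with no post-baseline reading should be counted and covered by the sensitivity analysis.
- **Terms:** baseline body fat, PUSH, activity level, visit and PUSH × visit.
- **Visits:** the available post-baseline readings. An unstructured covariance over 24 weekly visits has 24 × 25/2 = 300 parameters, too many for 90 women. Either specify a structured covariance for the weekly data, or use months 3 and 6 with chosen intermediate weeks. A four-weekly grid, for example, has 6 visits and 6 × 7/2 = 21 parameters.
- **Primary estimate:** the PUSH contrast at week 24, with its 95% confidence interval.
- **Sensitivity:** one analysis that assumes worse outcomes for women who drop out than the model predicts, with the size of the penalty fixed in advance.

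The cost is revised analysis wording and slightly more programming; no new visits, participants or data are needed. The model relies on missing at random, which is why the sensitivity analysis belongs with it.

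### No analysis of the PUSH effect is named as primary, and the ANCOVA is given the task of estimating the effect of baseline rather than of PUSH given baseline

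*Protocol article*

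**What the plan says.** The Sample size calculation section sets the target: "The primary outcome variable was fat mass loss after six months". It continues that "the anticipated minimum difference in the average fat mass loss was 2" per cent, "with an expected SD not exceeding 3.5" per cent.

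The Statistical analysis section then lists these methods:

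- **t test.** "For the bivariant hypothesis contrast, the two-means Student-t test was made". No covariates are mentioned.
- **Repeated-measures ANOVA.** "the ANOVA repeated means test was used to evaluate the effects of the intervention at the baseline moment, at 3 and 6 months". Baseline is one of the levels, and no group-by-time term is named.
- **ANCOVA.** "The ANCOVA analysis of covariance was applied to determine the effect of the baseline data on the modification of body composition". Its declared target is the baseline effect.
- **Adjusted linear regressions.** These model body fat, muscle mass and weight at the end of the study and are meant to estimate the PUSH effect as a standardised coefficient. The text does not say that the baseline value is among the covariates.

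One threshold, "an alpha error probability of under 5" per cent, applies to all analyses. None is singled out as primary.

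**The concern.** The trial asks whether PUSH notifications increase fat loss over six months. An ANCOVA answers that well when it estimates the group difference given baseline body fat. As printed, it estimates how baseline relates to change, which is another question.

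The methods that do address PUSH need not agree. The t test on loss, the repeated-measures ANOVA and the regression on final values have different precision. In the ANOVA the answer also depends on which term is read. All women follow the same hypocaloric diet, so the time effect mainly reflects the diet. The group main effect averages in a visit at which randomised groups cannot differ through treatment. A standardised coefficient is not on the percentage scale of the difference used to size the trial.

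With no order among the methods and 5% for each, the headline result could be chosen after the data are seen, and the most precise estimator is not clearly assigned to the treatment effect.

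**Working it through.** **Inputs from the protocol article.** Difference 2, SD 3.5, 27 per group required and 45 per group recruited (Sample size calculation). Significance level 5% (Statistical analysis). The sample-size section prints "at least an 80% power and an alpha level set at 0.5"; I use 0.05, two-sided.

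**Assumptions.** The 2 and 3.5 are percentage points of body fat, and 3.5 is the SD of the change, since it is attached to fat loss. The baseline-to-week-24 correlation ρ is not given; I use 0.5 to 0.8. Visits have equal variance σ² and equal correlation. The effect at 3 months is not given; I use 1 point.

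**The plan's own figure.** A two-group comparison needs n = 2 × (1.96 + 0.842)² × 3.5² / 2² = 48.1, so 49 per group. The stated 27 is not reproduced. It appears only as a two-sided one-sample or paired t test (26.02, rounded up). That is a separate matter; I show power at both 27 and 45.

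**Change-score t test.** SE = 3.5 × √(2/n). At 45 per group this is 0.738, and 2/0.738 = 2.71. At 27 it is 0.953, and 2/0.953 = 2.10. Power by the noncentral t is 0.76 and 0.54.

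**ANCOVA for PUSH.** The change variance is 2σ²(1 − ρ) = 12.25 and the ANCOVA residual variance is σ²(1 − ρ²), so the ratio is (1 + ρ)/2: 0.75 at ρ = 0.5 and 0.90 at ρ = 0.8. The effective SD is 3.5 × √0.75 = 3.03, or 3.5 × √0.90 = 3.32. Power is 0.87 and 0.81 at 45 per group, and 0.66 and 0.58 at 27. A simulation of 20,000 trials per setting gave 0.87 and 0.80, and 0.65 and 0.57.

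**Group-by-time test.** Here σ²(1 − ρ) = 12.25/2 = 6.125. With effects 0, 1, 2 the squared deviations from their mean sum to 2, so the noncentrality is (n/2) × 2 / 6.125 = n/6.125: 7.35 at 45 and 4.41 at 27. With 2 and 176 (or 104) degrees of freedom, power is 0.67 and 0.44, whatever ρ is.

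**Regression on the final value, if baseline is not a covariate.** With no other useful covariate, the SD is 3.5/√(2(1 − ρ)): 3.50 at ρ = 0.5 and 5.53 at ρ = 0.8. Power at 45 per group is 0.76 and 0.40. If baseline is a covariate, the ANCOVA figures apply.

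**Group main effect of the ANOVA, only if that term were read.** The averaged effect is (0 + 1 + 2)/3 = 1.0 with baseline and (1 + 2)/2 = 1.5 without it. With baseline included, the SD of a woman's three-visit mean is √(σ²(1 + 2ρ)/3): 2.86 and 5.15. Power at 45 per group is 0.38 and 0.15.

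| Analysis of PUSH | 45 per group | 27 per group |
|---|---|---|
| ANCOVA, ρ 0.8 to 0.5 | 0.80–0.87 | 0.58–0.66 |
| t test on change | 0.76 | 0.54 |
| Group-by-time | 0.67 | 0.44 |

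**The case against.** The strongest reply is that the section already contains the right analysis. It plans adjusted regressions of final body fat expressly to estimate the PUSH coefficient. If baseline body fat is a covariate, that is an ANCOVA for PUSH in all but name, and a journal article may leave the covariate list to a fuller plan. This stands. A reader might infer that the PUSH effect is left wholly to the unadjusted t test and the ANOVA; the text does not support that. The missing covariate list alone is no finding. What remains is what the article does state: baseline is assigned to a separate ANCOVA with another aim, and the methods carry no order.

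Second, a repeated-measures ANOVA that includes baseline is legitimate when group-by-time is read, which is the usual intervention test. This also stands. A reader might infer that the ANOVA is invalid, or has power of only 0.15 to 0.38. That applies to the group main effect, which the protocol does not say it will use. Nor does including baseline halve the effect: it lowers the average from 1.5 to 1.0, and the rest of the gap from 2.0 comes from the assumed 1 point at 3 months. Nothing in the text says that the time effect will be presented as the PUSH effect.

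Third, the primary outcome is a loss, so a t test on it already uses baseline and is valid under randomisation. True; the cost is efficiency.

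Finally, 45 per group is the recruited number, inflated for dropout, so power at 45 is a best case. Hence the figures at 27.

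**Conclusion.** The point holds in a limited form. The section gives at least three routes to the PUSH effect at 5% each, names none as primary, and states the ANCOVA's purpose as the effect of baseline on change. That sentence may be loose wording for a baseline-adjusted comparison. If so, it should be corrected, because as printed it describes a different estimand.

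The efficiency at stake is moderate: the ANCOVA variance is 10 to 25% below that of the change score for ρ from 0.8 to 0.5. At 45 per group this takes power from 0.76 to 0.80–0.87, against 0.67 for group-by-time. If the final-value regression did omit baseline, the loss could be larger, down to 0.40 at ρ = 0.8. These figures rest on the assumed correlations, equal variances, a change SD of 3.5 and, for group-by-time, 1 point at 3 months. No inflation of the type I error has been computed; the concern there is freedom of choice among analyses. It should be settled before analysis, but it does not invalidate any listed test.

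**What to change.** Restate the ANCOVA, or equally the adjusted regression, as the single primary analysis: body fat at week 24 on PUSH group, randomised activity level and baseline body fat. Report the adjusted mean difference in percentage points with its 95% confidence interval, so that it can be set against the 2 points used for sizing. Standardised coefficients may be added as a secondary description.

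Read any repeated-measures ANOVA through the group-by-visit contrast, not the time effect or the group main effect. Label the t test, the ANOVA and the remaining regressions as supportive. If the relation of baseline to change is of interest in itself, list it as a separate exploratory question.

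The cost is a few sentences in the analysis section. The baseline measurement and the activity allocation are already collected, and no change to recruitment or visits is needed.
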